## Abstract

**Background:**

Surgical site infection (SSI) is a common complication following abdominal surgery. It is associated with considerable morbidity and mortality, and its management results in significant cost to health services within both primary and secondary care. Some surgeons believe that the use of a wound-edge protection device may reduce the incidence of SSI. Whilst there is some encouraging evidence showing that such devices may lead to a reduction in SSI, there are no controlled trials of sufficient size or quality to support their routine use.

**Methods/Design:**

750 patients will be recruited from around 20 surgical units within the United Kingdom. Patients undergoing laparotomy through any major abdominal incision for any indication, elective or emergency, are eligible. Patients under the age of 18, those undergoing a laparoscopic assisted procedure or who have undergone laparotomy within the previous 3 months, and those who are unable to give informed consent will be excluded. Patients will be randomised (1:1 ratio) to the use of a wound-edge protection device or no wound-edge protection device during surgery.

Follow up will consist of blinded clinical wound reviews at 5-7 days and 30-33 days postoperatively with a self-completed questionnaire covering the intervening period. Quality of life questionnaires will be completed prior to surgery and at the subsequent wound review points and information on resource usage will also be captured.

The primary outcome measure is SSI within 30 days of surgery. Secondary outcomes include the impact of the degree of wound contamination, patient comorbidity, and operative characteristics on the efficacy of a wound-edge protection device in reducing SSI and whether the use of a wound-edge protection device has an effect on health-related quality of life or length of hospital stay and is cost-effective.

**Discussion:**

Rossini is the first multicentre observer-blinded randomised controlled trial of sufficient size and quality to establish whether the use of a wound-edge protection device in adult patients undergoing abdominal surgery leads to a lower rate of SSI. The results of this study will be used to inform current surgical practice and may potentially benefit patients undergoing surgery in the future.

**Trial registration number:**

Current Controlled Trials ISRCTN: ISRCTN40402832

## Background

Surgical site infection (SSI) is one of the most common postoperative complications and occurs in at least five percent of all patients undergoing surgery [1]. The rate of SSI is significantly higher after open abdominal surgery which can carry an SSI risk of up to 40% depending on the level of contamination [2].

SSI is associated with considerable morbidity and it has been reported that over one-third of postoperative deaths are related, at least in part, to SSI [3]. It must be appreciated, however, that the diagnosis covers a wide spectrum of clinical conditions ranging from a relatively trivial wound discharge with no other complications to a life-threatening condition. Other clinical outcomes of SSI include poor scars that are cosmetically unacceptable, such as those that are hypertrophic or keloid, persistent pain and itching and a significant impact on emotional wellbeing [4].

SSI can double the length of time a patient stays in hospital and thereby increase the costs of health care. Additional costs attributable to SSI of between £814 and £6626 per case have been reported depending on the type of surgery and the severity of the infection [5,6]. The main additional costs are related to re-operation, extra nursing care and interventions, and drug treatment costs. The indirect costs, due to loss of productivity, patient dissatisfaction and litigation, and reduced quality of life, have been studied less extensively.

Recent national guidelines concerning the prevention and treatment of SSI have been issued by the National Institute for Health and Clinical excellence (NICE) [7]. These recommendations are based on systematic reviews of best available evidence, or when minimal evidence is available the guideline development group's opinion of what constitutes good practice. Intra-operative guidance includes the role of hand decontamination, sterile gowns and drapes and antiseptic skin preparation. Wound-edge protection devices are not discussed in these guidelines, presumably due to the paucity of published research into their use and efficacy in the prevention of infection

It is notable that some adhesive plastic 'incise' drapes, favoured by some surgeons, are not recommended in the guidelines. A recent Cochrane review and meta-analysis found that they may increase the chance of an SSI [8]. Iodine-impregnated incise drapes fare better (in terms of no added risk) but still do not offer a significant improvement in wound infection rate compared with no drape at all.

### Wound-edge protection devices

Some surgeons advocate the use of a wound edge protector or 'wound guard' to reduce SSI. There are several different devices on the market but they all share the same basic design - a semi-rigid plastic ring placed into the abdomen via the laparotomy wound to which an impervious drape is circumferentially attached. This plastic drape comes up and out of the wound onto the skin surface, thus protecting the cut wound edges. The proposed mechanism of action of the device is two-fold. Firstly, they create a physical barrier between the abdominal wound edges and viscera, visceral contents, contaminated instruments and gloves - thus reducing accumulation of endogenous and exogenous bacteria on the wound edges. They also potentially reduce tissue necrosis from long procedure exposure as well as performing a degree of mechanical retraction which in turn may reduce the need for handheld mechanical retraction and the tissue damage associated therein. Smaller versions of wound-edge protection devices are also currently often used in laparoscopic-assisted resections of colorectal malignancies to prevent seeding of tumour cells into wound edges.

As mentioned above, these devices were not considered at all in the NICE guidelines and there has been minimal formal research evaluating their value. Two recent descriptive studies of their use failed to provide strong conclusions [9,10]. More encouragingly, two separate small randomised controlled trials (RCTs) comparing use of the device against standard treatment did show encouraging results [11,12], with a variable rate of reduction of up to 84% depending on degree of wound contamination. However, the trials were both single-centre and not without some shortcomings in design, in particular relating to randomisation strategy, blinding of researchers and follow-up protocols. All other research into the devices is over 25 years old and assesses older-generation devices in a different era to that of today in terms of the background advances in infection prophylaxis. Table 1 summarises the published data on the usage of wound-edge protectors [9-16]. There is no systematic review or meta-analysis of the use of a wound-edge protector. This probably accounts for the limited uptake of the device amongst the general surgeons of today. The highest level of evidence regarding the devices probably comes from a review of the Sookhai RCT [11] in the Evidence-Based Medicine journal soon after its publication [17]; the conclusion of this review was that whilst there was evidence that the device reduced SSI (particularly in operations with a higher level of contamination), wider application of the device should await the result of a more rigorously designed multicentre study.

**Table 1 T1:** Summary of published data on wound edge protection devices

Lead Author	Year of Publication	Title	Type of Study	Comments
Horiuchi [12]	2007	Randomised, controlled investigation of the anti-infective properties of the Alexis retractor/protector of incision sites	**RCT**; 2 arms - control vs. wound-edge protector	Looks well-designed 221 patients Positive results Single centre

Kercher [9]	2004	Plastic wound protectors do not affect wound infection rates following laparoscopic-assisted colectomy	Retrospective review	Descriptive study only 141 patients Laparoscopic cases

Nakagoe [10]	2001	Minilaparotomy wound edge protector (Lap-protector): a new device	Description of technique	Descriptive study only No comparison group

Sookhai [11]	1999	Impervious wound-edge protector to reduce postoperative wound infection: a randomised, controlled trial	**RCT**; 2 arms -control vs. wound-edge protector	Looks well-designed 352 patients Positive results Single centre

Nystrom [13]	1983	A controlled trial of plastic wound ring drape to prevent contaminations and infection in colorectal surgery	**RCT**; 2 arms - control vs. wound-edge protector	140 patients No benefit found Old-generation device

Psaila [14]	1977	The role of plastic wound drapes in the prevention of wound infection following abdominal surgery	**RCT**; 3 arms - control vs. adhesive drape vs. wound-edge protector	154 patients No benefit from either device Poor follow-up

Alexander -Williams [15]	1972	Abdominal wound infections and plastic wound guards	**RCT**; 2 arms - control vs. wound-edge protector	167 patients Poor follow-up to 10 days only Inconsistent design

Maxwel [16]	1969	Abdominal wound infections and plastic drape protectors	Comparative study	No randomisation Poorly designed study 202 patients

### Issues relating to a potential randomised controlled trial of wound-edge protectors

1 No multicentre trial has been done

2 No current data explores efficacy in prevention of early versus late SSI

3 No current data explores pathogen bias in SSI prevented (or not prevented) by the device

We propose a prospective multicentre randomised controlled trial that will address all of these issues.

### Primary Hypothesis

Use of a wound-edge protection device in adults undergoing laparotomy will result in a reduced rate of surgical site infection (SSI).

## Methods/Design

### Study Design

A prospective, multicentre, observer blinded, randomised controlled trial with stratification according to baseline infection risk

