### Primary outcome measure

The primary outcome is Surgical Site Infection (SSI) within 30 days of surgery.

Positive identification of SSI will be determined with use of the internationally accredited Centers for disease Control and Prevention (CDC) definitions.

We hypothesise that the use of wound-edge protection device in adults undergoing laparotomy will result in a reduced rate of surgical site infection of 50% based on evidence from Horiuchi et al, 2007 [12].

The power calculations for a range of baseline infection rates and this assumed 50% reduction in SSI rate brought about by use of the device are shown in table 2.

**Table 2 T2:** Infection rates and sample size

Infection rate in untreated group	Expected infection rate in treated group	Overall sample size	Sample size in each arm
18%	9%	448	224

15%	7.5%	554	277

12%	6%	**710**	**355**

(80% power and 0.05 significance level)

A conservative estimate of infection rate of 12% requires a total of 710 patients, randomised 1:1 between treatment and placebo. Thus we intend to recruit 750 patients in total in order to provide adequate power should our assumptions informing the power calculation prove optimistic, and to accommodate a potential 5% dropout rate.

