### Trial Management Protocols

Two named principle investigators (PI) will be recruited at each study site. Together they shall provide blinded wound reviews for the other PI's patients by being unaware of which arm of the study these patients belong to. The two wound reviews will occur firstly prior to discharge at day 5 to 7 post-operation and then a formal outpatient appointment or ward attendance for wound review will be arranged at or just after 30 days (day 30-33 post-operation). At this visit patients will also be asked to complete a retrospective questionnaire regarding their wound and its healing over the intervening period. This will ensure that full information is gathered about any wound infections, together with resulting treatment or hospital admissions, occurring between the day 5-7 and day 30-33 reviews. Enrolled patients will also be given contact details for the local primary investigator should any concerns by raised by the patient. Wound assessment at both stages will utilise a standardised proforma. These wound assessment tools will be pre-validated for reproducibility and ease-of-use in a pilot study to be ran prior to full trial launch.

QOL data will be assessed using the EQ-5D pre-operatively, at 5-7 days, at the 30-33 day follow-up visit.

We also envisage the involvement of clinical nurse specialists at most sites. Their clinic appointments are generally more accessible and it may be feasible to utilise these for the second formal (outpatient) wound review. Clinical nurse specialists are generally experienced in assessing post-operative wounds themselves and they may also therefore provide a second-line cohort of blinded wound reviewers if the relevant PI is not available.

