**Figure 1 F1:**
[figure not shown]
**Flowchart Illustrating Study Process**.

1. Informed consent for participation in the study is obtained preoperatively, ideally at the same setting where (normal) consent for the intended surgical procedure is obtained > 24 hrs prior to surgery (except in an emergency setting). Patients will ideally have been previously given a patient information sheet at the time of listing for their operation.

2. After induction of anaesthesia at the time of surgery the patient is allocated to either the wound-edge protector group or the control (no protector) group by the surgeon, using a secure 24 hour internet-based randomisation service - provided by the UKCRC Accredited Primary Care Clinical Trials Unit, University of Birmingham.

3. Normal local policy for systemic antibiotic prophylaxis is followed.

4. Standard routine skin preparation is undertaken according to local policy.

5. Antiseptic-soaked towels on wound edges may also be used in either group.

6. The operation is carried out as normal, with removal of the wound guard (if applicable) as late as possible prior to wound closure.

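### Nothing in the design keeps patients unaware of their arm, although their own report contributes to the primary outcome between the two blinded wound reviews

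*Protocol article*

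**What the plan says.** The Study Design section labels the trial: "A prospective, multicentre, observer blinded, randomised controlled trial with stratification according to baseline infection risk". Trial Management Protocols explains how this is achieved. Each site has two principal investigators, and "Together they shall provide blinded wound reviews for the other PI's patients by being unaware of which arm of the study these patients belong to". Clinical nurse specialists may stand in as blinded reviewers. No blinding procedure is described for anyone else.

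On the outcome, Primary outcome measure states: "The primary outcome is Surgical Site Infection (SSI) within 30 days of surgery". It adds: "Positive identification of SSI will be determined with use of the internationally accredited Centers for disease Control and Prevention (CDC) definitions". The Abstract gives the sources of information: "Follow up will consist of blinded clinical wound reviews at 5-7 days and 30-33 days postoperatively with a self-completed questionnaire covering the intervening period". Trial Management Protocols places the questionnaire at the second review: "At this visit patients will also be asked to complete a retrospective questionnaire regarding their wound and its healing over the intervening period". Its stated purpose is complete capture of wound infections, and of the treatment or admissions that followed, between the two reviews. EQ-5D is completed before surgery and at both review points.

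On timing, step 2 of Study Process reads: "After induction of anaesthesia at the time of surgery the patient is allocated to either the wound-edge protector group or the control (no protector) group". Step 6 has the device removed before the wound is closed.

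**The concern.** The reviewers' blinding protects what the reviewers see. An infection that starts after the first review and has healed by the second is never seen by a blinded reviewer under the scheduled follow-up, so it reaches the trial through the patient's account. The Background notes that SSI extends down to trivial wound discharge, and reports of mild events like that are open to expectation. EQ-5D is the named quality-of-life measure, and the economic analysis reports cost per QALY.

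A patient who learns after surgery whether a wound guard was used could therefore affect three things: the interval component of the primary outcome, the EQ-5D scores, and the reviewer's own blinding if the patient mentions the arm at a review. The design does not close this route, although it has the features that would allow it to.

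**Working it through.** **1. Where self-report enters.** The reviews fall on days 5-7 and 30-33. The gap between them is at least 30 − 7 = 23 days and at most 33 − 5 = 28 days. An infection present at either review is open to blinded assessment. One that arises and resolves within the gap depends on the questionnaire. Self-report therefore supplies part of the primary outcome. The document does not give the share.

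**2. The plan's own sample size.** Inputs from Primary outcome measure: 12% v 6%, 80% power, significance level 0.05 (taken as two-sided), 1:1 allocation.

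n per arm = [1.96·√(2·0.09·0.91) + 0.8416·√(0.12·0.88 + 0.06·0.94)]² / 0.06² = (0.7932 + 0.3387)² / 0.0036 ≈ 356

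That is 712 in total, against the stated 710, so the figure reproduces. After 5% dropout, 750 × 0.95 = 712.5, or about 356 per arm, which is used below. Blinding patients alters none of these figures.

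**3. What a reporting gap could do.** Everything in this step except the 12% and the 356 is assumed. There is no true effect, and both arms have 12% SSI. Let s be the share of infections known only from the patient. With observed rates p_C (control) and p_T (device), and p̄ their mean:

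SE = √(2·p̄·(1 − p̄)/356)

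false-positive rate = Φ(|p_C − p_T|/SE − 1.96) + Φ(−|p_C − p_T|/SE − 1.96)

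This is a simple comparison of two proportions. It ignores the surgeon effect and the interim analyses.

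*Set A.* Device patients under-report a fraction b of the self-report-only infections, so p_T = 0.12(1 − s·b) and p_C = 0.12. In the "both" columns controls also over-report by the same fraction, so p_C = 0.12(1 + s·b).

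| s | b | p_T | Risk ratio | False-positive rate | Risk ratio, both | False-positive rate, both |
|---|---|---|---|---|---|---|
| 0.2 | 0.1 | 0.1176 | 0.98 | 5.1% | 0.96 | 5.4% |
| 0.4 | 0.2 | 0.1104 | 0.92 | 6.9% | 0.85 | 12.4% |
| 0.6 | 0.3 | 0.0984 | 0.82 | 15.2% | 0.70 | 42.6% |

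*Set B.* Controls report 90% and device patients 80% of the self-report-only infections (r). Uninfected patients falsely report at rate f. Observed rate = 0.12·[(1 − s) + s·r] + 0.88·f.

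| s | f, control v device | p_C | p_T | Odds ratio | False-positive rate |
|---|---|---|---|---|---|
| 0.3 | 0 v 0 | 0.1164 | 0.1128 | 0.96 | 5.3% |
| 0.5 | 0 v 0 | 0.1140 | 0.1080 | 0.94 | 5.7% |
| 0.3 | 5% v 3% | 0.1604 | 0.1392 | 0.85 | 12.4% |
| 0.5 | 5% v 3% | 0.1580 | 0.1344 | 0.83 | 14.5% |

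In the last two rows the assumed over-reporting gap contributes 0.88 × 0.02 = 0.0176 of the arm difference. That is 0.0176/0.0212 = 83% at s = 0.3 and 0.0176/0.0236 = 75% at s = 0.5. Without it, the recall difference leaves the error rate close to nominal.

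**4. Direction.** Both sets were built so that misreporting favours the device. Exchanging the arms gives the same false-positive rates with the apparent effect reversed.

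**The case against.** The strongest reply is that silence is not a decision. The article nowhere says that patients are told their arm. That would normally be settled in the patient information sheet or the full protocol, neither of which is shown. With allocation under anaesthesia and no device left in place, a patient learns the arm only if someone discloses it. This stands as a limit: a reader might infer that patients will be told, and the document does not support that. The point survives because the article states its level of blinding, how the blinding is done and the steps of the study process, and all of these place it with the wound reviewers. A site following the text would have no reason to withhold allocation.

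Second, a reader might infer that the primary outcome rests on self-report, or that the observer-blinded label is false. Neither follows. SSI is determined by CDC definitions, there are two blinded reviews on a standard form, and the questionnaire also asks about treatment and admissions, which are more concrete than an opinion of the wound. No section says that an unconfirmed questionnaire entry counts as an SSI. The label is accurate for the reviews to which it is attached. Even so, applying CDC definitions to a healed episode depends on the history that the patient gives.

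Third, it is tempting to quote a 12-14% error rate and to say that the bias favours the device. Most of that figure comes from an over-reporting gap that nothing in the document supports. The direction is likewise an assumption: patients who know that they had a trial device might watch the wound more closely and report more.

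**Conclusion.** The concern holds in limited form. Blinding is described for observers only, no section keeps patients unaware, and patient report contributes to the primary outcome for infections that arise and resolve between reviews, as well as supplying EQ-5D. This is an avoidable route of bias rather than a demonstrated one. It operates only if patients learn their arm and report or talk differently as a result.

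Its size depends on three quantities that the document does not give: the share of infections known only from patients, the reporting gap between arms, and how questionnaire episodes are confirmed. Across the assumed values the effect runs from negligible to material. The recommendation rests on how easily the route can be closed, not on any single error rate.

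**What to change.** Amend Study Design and Study Process so that the trial is patient- and observer-blinded:

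- Tell patients at consent that they will not learn their allocation until the day 30-33 wound review, questionnaire and EQ-5D are complete. Allow unblinding on clinical need.
- Ask theatre and ward staff not to disclose the arm to the patient.
- State that an episode known only from the questionnaire is judged by the blinded reviewer against the CDC definitions that the protocol already names.
- Optionally, ask patient and reviewer at day 30-33 whether they know the allocation.

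The cost is small but not nil: wording in the protocol and information sheet, a request to staff, perhaps one item on the day 30-33 form, and a wait of about a month before patients learn their allocation. No sham procedure, extra visit, extra staff or change in sample size is needed.

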### Study Setting

The study will take place in general surgical units within the NHS. Surgical units in the West Midlands are being approached as are units in London, Southampton, Plymouth and Trent. Twelve sites are being identified to collaborate in the trial initially.

### Ethical Approval

Full ethical approval has been gained from the North Staffordshire Research Ethics Committee (ref: 09/H1204/91).

### Inclusion Criteria

All adults undergoing laparotomy via midline, transverse or Kocher's incision (for any surgical indication), including both elective and emergency operations

